## Abstract

**Background:**

Chronic obstructive pulmonary disease (COPD) is a chronic inflammatory lung disease characterized by coughing, the production of excess sputum, and dyspnea. Patients with excessively thick sputum may have frequent attacks or develop more serious disease. The guidelines recommend airway clearance for patients with excessive sputum who are hospitalized with COPD. The active cycle of breathing technique is the most common non-pharmacological airway clearance technique used by physiotherapists. However, the effectiveness of the technique is not always guaranteed. Active cycle of breathing techniques require the initial dilution of the sputum, usually by inhalation drugs, which may have limited effects. Recent studies have found that phonophoresis decreases inflammation, suggesting the potential of the combined usage of active cycle of breathing techniques and phonophoresis. Therefore, the aim of this study is to explore the effectiveness and safety of combining active cycle of breathing technique and phonophoresis in treating COPD patients.

**Methods and analysis:**

We propose a single-blind randomized controlled trial using 75 hospitalized patients diagnosed with COPD with excessive sputum production. The patients will be divided into three groups. The intervention group will receive active cycle of breathing techniques combined with phonophoresis. The two comparison groups will be treated with active cycle of breathing techniques and phonophoresis, respectively. The program will be implemented daily for 1 week. The primary outcomes will be changes in sputum viscosity and production, lung function, and pulse oximetry. Secondary outcomes include the assessment of COPD and anxiety, measured by the COPD Assessment Test scale and the Anxiety Inventory for Respiratory Disease, respectively; self-satisfaction; the degree of cooperation; and the length of hospital stay. All outcome measures, with the exception of sputum production and additional secondary outcomes, will be assessed at the commencement of the study and after 1 week’s intervention. Analysis of variance will be used to investigate differences between the groups, and a *p*-value of less than 0.05 (two-tailed) will be considered statistically significant.

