#### Primary outcomes

The first primary outcome will be sputum viscosity calculated using a viscometer [29, 30]. After the collection of sputum from patients, in line with the instructions, the assistant will insert the sputum into the rotor in the viscometer and read the digital output. The sputum viscosity is calculated by the formula (sputum viscosity = viscometer reading × 10). Patients will be given calibrated containers [31] at the baseline visit and instructed to collect 24 h worth of sputum in the container, between 07:00 each morning and 07:00 the following morning. The outcome assessor will observe and record the volumes of sputum at the 1- and 24-h time points daily during the intervention period.

We hope to reduce obstruction by clearing the sputum in the respiratory tract. Therefore, we will use the same pulmonary function meter to perform a complete spirometry assessment before and after the intervention [32]. Vital capacity can reflect the obstruction of pulmonary function and airway obstruction will be determined by FEV_1_%. The relation between expiration in the first second of forced expiration (FEV_1_) and the full forced vital capacity (FVC) will be represented by FEV_1_%, with normal values being approximately 75%. Generally speaking, the FEV_1_% of COPD patients is less than 70%. We are investigating whether this can be improved. The outcome assessor will only record vital capacity and FEV_1_% from the spirometry. We will follow the recommendations of the American Thoracic Society and European Respiratory Society [33] in the lung function test. Patients will be assessed between three and eight times, and the three best measurements with variability of less than 5% or 200 ml will be recorded [34]. The oxygen saturation of COPD patients will be expressed as SpO_2_. Similarly, SpO_2_ will be determined by pulse oximetry from the right middle finger [35–37] before and after the intervention. Since SpO_2_ is also a variable parameter, the patient will receive three evaluations and the average of the results recorded.

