### Data collection, management, and analysis

All patients’ data will be recorded by trained clinical researchers using a standardized case report form (CRF) and saved using the EpiData electronic database. To ensure the reliability of our study, the management of this trial will be conducted by the Trial Steering Committee (TSC). Main investigators and statisticians consist of our Trial Steering Committee, who will oversee the entire trial. Meetings will be held once a month to monitor the progress of the research and to share opinions when there are problems. The measurement data will be expressed by mean ± SD, and the count data will be expressed by frequency and percentage. A Kolmogorov-Smirnov test will be performed to analyze sample normality. Within-group changes in sputum viscosity, FEV_1_%, vital capacity, arterial oxygen saturation, quality of life, and the level of anxiety will be compared using a paired *t*-test or Wilcoxon test depending on the data distribution. Inter-group differences between baseline and post-intervention among the outcomes will be compared by one-way analysis of variance. According to the normality of the data distribution, a general linear model or multi-generalized linear model will be used to compare the differences between the primary and secondary outcomes after adjusting the covariates, including sociodemographic variables, such as sex, age, body mass index, smoking history, severity of disease, among others, and baseline variables. In addition, we will follow the principle of intention to treat (ITT) and use the sequence mean method to deal with the missing data to analyze the results of the comparison between groups of each outcome. To assess whether the missing data will affect the results of the study, we will compare participants who did not complete the intervention with those who completed the intervention to verify the sensitivity of the results of the trial. A two-tailed *p*-value of < 0.05 will be taken as significant. The data from this experiment will be entered by Epidata3.1 and analyzed by SPSS 26.0 software.

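### At least five primary variables share one uncorrected 0.05 threshold with no stated success rule, while only sputum viscosity is sized

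*Protocol article*

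**What the plan says.** The Abstract (Methods and analysis) lists four headings without ranking them: "The primary outcomes will be changes in sputum viscosity and production, lung function, and pulse oximetry".

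The Primary outcomes section gives the detail. It opens with viscosity: "The first primary outcome will be sputum viscosity calculated using a viscometer". For sputum production, the assessor is to "record the volumes of sputum at the 1- and 24-h time points daily during the intervention period". Lung function becomes two variables: "The outcome assessor will only record vital capacity and FEV_1_% from the spirometry". SpO2 is described in the same section.

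One decision threshold is given. The Abstract says that a *p*-"value of less than 0.05 (two-tailed) will be considered statistically significant", and the data analysis section repeats it: "A two-tailed *p*-value of < 0.05 will be taken as significant". That section compares the arms on the outcomes by one-way analysis of variance and adds covariate-adjusted models.

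The Sample size section is for sputum viscosity only: 90% power, alpha 0.15, effect size 0.4, 20% dropout, 75 patients in three arms of 25.

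**The concern.** Several outcomes hold primary status together, and each can be declared significant at the same 0.05. Nothing in the article says whether one positive result is enough, whether all are needed, or whether the other tests depend on viscosity. The 0.05 level is therefore the error rate of a single test and not of the primary conclusion.

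A simple case shows what is at stake. Viscosity, the only sized outcome, shows no difference, but SpO2 gives *p* = 0.04. Nothing in the text prevents that from being reported as a positive primary result. The Discussion says that a demonstration of effectiveness could make the combined programme a better treatment for COPD, so readers need to know what would count as a demonstration.

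**Working it through.** **1. The plan's own figure.** Inputs from the Sample size section: 3 arms, alpha 0.15, power 90%, effect size 0.4 (read as Cohen's f, an assumption), dropout 20%. With 20 evaluable per arm (N = 60), the noncentrality is N × f² = 60 × 0.16 = 9.6, and the power of the overall F test is 90.5%. Dropout: 20 / (1 − 0.20) = 25 per arm, and 3 × 25 = 75. The stated total is reproduced, for viscosity alone.

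**2. Counting the family.** Viscosity, sputum production, vital capacity, FEV1% and SpO2 make five. This is a minimum, because production is recorded at two time points each day.

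**3. Familywise error, independent outcomes.** Assume no true difference on any outcome, one overall analysis of variance per outcome at 0.05, and success if any one is significant.

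- Five variables: 1 − 0.95⁵ = 1 − 0.774 = 22.6%.
- Four variables: 1 − 0.95⁴ = 1 − 0.815 = 18.5%.

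**4. Familywise error, correlated outcomes.** The article gives no correlations, so a range is shown. Simulation used equicorrelated normal outcomes, three arms of 20 and 40,000 runs per setting:

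| Correlation | Five variables | Four variables |
|---|---|---|
| 0 | 22.4% | 18.6% |
| 0.2 | 21.8% | 18.0% |
| 0.3 | 21.3% | 17.6% |
| 0.5 | 19.0% | 15.9% |
| 0.7 | 15.3% | 13.6% |
| 0.8 | 13.4% | 11.8% |

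The simulation error is about 0.2 percentage points: √(0.2 × 0.8 / 40,000) = 0.002.

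**5. Power under the possible repairs** (viscosity, f = 0.4):

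| Threshold | 20 evaluable per arm | 25 evaluable per arm |
|---|---|---|
| 0.05 (single primary) | 77.6% | 86.9% |
| 0.01 = 0.05 / 5 (Holm's first step) | 54.4% | 68.4% |

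For 90% power at 0.01, 38 evaluable per arm are needed. After 20% dropout this is 38 / 0.8 = 47.5, so 48 per arm and 144 in total.

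**The case against.** **The success rule is not written down.** A reader might infer that the plan lets any one significant result count as success and so carries a false-positive chance of about 20%. The article does not say so. If all five had to be significant, the familywise rate would not exceed 5%. This stands: the figures are conditional on the any-one reading, and a value near 20% also needs low to moderate correlation.

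**A higher figure is not supported.** Counting the 1-h and 24-h volumes as separate outcomes gives 1 − 0.95⁶ = 26.5%. That treats two volumes measured in the same patients on the same days as independent, which is implausible. One can say only that repeated volumes would raise the rate.

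**The test of sputum production is partly inferred.** The list of within-group comparisons omits production, and production has its own assessment schedule. It falls under the analysis of variance only through the general reference to the outcomes. Without it, four variables remain, with 18.5% under independence. The problem is smaller but still there.

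**A condensed article may leave multiplicity to the analysis plan.** This is fair for technical detail. But the article itself fixes several primary outcomes and one flat threshold, and a later correction would have to depart from that stated rule.

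**Viscosity is called first, and the aim is worded as exploratory.** The word *first* opens a list; no other test is made to depend on viscosity, and the Abstract does not rank the outcomes. The exploratory wording softens the point, but the plan also names primary outcomes, a power target and a significance rule.

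**Conclusion.** The point holds in conditional form. The article fixes at least five primary variables at an uncorrected 0.05, does not say what counts as primary success, and sizes only one of them. The false-positive rate of the primary conclusion is thus undefined and uncontrolled, which is more than a missing detail.

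If any one positive result suffices, the rate is 22.6% under independence and roughly 13% to 21% at correlations of 0.8 down to 0.3. Even the low end is more than two and a half times the nominal 5%. These figures cover only the five overall tests; unadjusted pairwise comparisons of the three arms would raise them, as would repeated sputum volumes.

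**What to change.** **Preferred.** By a dated amendment and a registry update, made before outcome data are analysed by arm, name the 1-week change in sputum viscosity as the single primary outcome. Report sputum production, vital capacity, FEV1% and SpO2 as secondary, with confidence intervals and no confirmatory claim. This matches the outcome already listed first and the only one sized, and it needs no extra patients for multiplicity.

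*Cost:* confirmatory claims on four outcomes are lost. The Trial status section says that recruitment has begun, so this is an endpoint change during the trial and must be dated and reported as one. Separately, the sizing used alpha 0.15: tested at 0.05, viscosity has 77.6% power with 20 evaluable per arm, not the stated 90%.

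**Alternative.** Keep all five as primary, with Holm across them and one stated analysis for each, including one summary measure of sputum production. *Cost:* about 54% power at the first step (0.01) with 20 evaluable per arm, or 68% with 25. Viscosity could still pass at a later, less strict step if other outcomes are rejected first, so these are lower bounds for it.

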**Discussion:**

This study introduces a combination of active cycle of breathing techniques and phonophoresis to explore the impact of these interventions on patients hospitalized with COPD. If this combined intervention is shown to be effective, it may prove to be a better treatment for patients with COPD.

**Trial registration:**

The trial was registered prospectively on the Chinese Clinical Trial Registry on 24 December 2019.ClinicalTrials.gov ChiCTR1900028506. Registered on December 2019.

## Article summary

Strengths and limitations of this study:
The use of phonophoresis in treating COPD patients is poorly documented.The combination of active cycle of breathing techniques and phonophoresis is novel.Study personnel are experienced physicians, rehabilitators, and caregivers, providing practical guidance for the research.We propose a single-center randomized clinical trial. It is unclear whether our findings will be generalizable to other locations and clinical settings. However, the large geographic, cultural, and socioeconomic diversity of the inpatients may help to reduce this potential bias.

## Introduction

According to the statistics of the Global Burden of Disease Study, chronic obstructive pulmonary disease (COPD) has a high prevalence, as well as high mortality and morbidity [1–7]. In China alone, in 2015, nearly 100 million people were suffering from COPD [8]. Furthermore, the medical expenses of patients with COPD are increasing, resulting in a heavier economic burden. At present, COPD has become a global public health problem.

Cough, sputum production, and dyspnea are the main symptoms of COPD [9, 10]. Patients with excessively thick sputum may suffer frequent attacks or be prone to more serious disease [11]. To address the problem of excessive viscous sputum in patients hospitalized with COPD, the American Association for Respiratory Care (AARC) published the “AARC clinical practice guideline: effectiveness of non-pharmacologic airway clearance therapies in hospitalized patients.” This guideline [12] describes the necessity for airway clearance in such patients. A cross-sectional survey [13] in Sweden showed that 75% of physiotherapists prescribed airway clearance treatments for most COPD patients, and most physiotherapists (89%) believe that sputum clearance is an important aspect of the overall management of COPD patients. Of the various non-pharmacologic airway clearance techniques, active cycle of breathing techniques are the most commonly used by physiotherapists [14]. A systematic review [15] shows that the active cycle of breathing technique can improve lung function, levels of arterial blood gases, perceived levels of dyspnea, and quality of life. In addition, the systematic reviews of Cabillic et al. [16] and Ides et al. [17] observed that the active cycle of breathing technique was an effective treatment for patients with COPD, with a grade B level of evidence, in comparison to other airway clearance techniques.

Both expectoration and reducing lung inflammation are necessary in treating COPD. Phonophoresis is a physical therapy technique that combines ultrasound and topical medications [18]. It has been proven to decrease inflammatory infiltration [19] through the absorption of ultrasonic energy and cavitation [20] and has been widely studied as a non-invasive method of medication administration [21]. There is ample evidence showing that phonophoresis is both more effective and leads to greater patient compliance [22] than conventional methods for administering medication. Recent studies have demonstrated the efficacy of phonophoresis in the treatment of acute calcific tendinitis of the shoulder [23], chronic nonbacterial prostatitis [24], and chronic rhinosinusitis [25], among other diseases. At present, COPD patients in the Medical Center in Changchun, China, mostly use inhalation therapy to dilute the sputum. We propose exploring the use of phonophoresis combined with active cycle of breathing techniques to relieve the respiratory symptoms of COPD patients, which may be more effective than the use of a single treatment. To our knowledge, there are no reports of the use of this combined therapy for COPD. The aim of this single-blind, three-arm, randomized controlled trial, therefore, is to investigate combining active cycle of breathing techniques and phonophoresis in treating patients hospitalized with COPD.

## Methods

### Study design

This is a single-blind, three-arm, randomized controlled trial. The intervention group will receive active cycle of breathing techniques combined with phonophoresis and control group 1 will receive active cycle of breathing only, while control group 2 will receive phonophoresis only. By comparing these three groups, we hope to explore the benefits of a combined program, compared to a single intervention. For the three-armed trial [26], COPD patients will receive active cycle of breathing techniques during hospitalization. Because the mean length of hospital stay for COPD patients in our medical center is 1 week, the duration of the intervention in our study will be set at 1 week. The trial will be conducted at the Medical Center in Changchun, China. In line with the recommendations of the Protocol Items Recommendations for Interventional Trials (SPIRIT) guidelines [27], our research protocol has been registered with the China Clinical Trial Registration (ChiCTR1900028506) and has been approved by the Ethics Committee of Jilin University (2019122301). We expect to begin recruitment in December 2019 and end in June 2021. Any changes to the plan will be negotiated with trial participants and the ethics committee. A copy of the revised protocol will be sent to the patient involvement branch of the ethics committee to add to the Investigator Site File, and any deviations from the protocol will be fully documented using a breach report form.

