### Groups

#### Intervention group: active cycle of breathing techniques combined with phonophoresis

These patients will receive both active cycle of breathing techniques and phonophoresis during the 1-week intervention period. The active cycle of breathing technique consists of three main components [15]: breathing control, a thoracic expansion exercise, and a forced expiration technique.

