##### Forced expiration technique

The physical therapist guides the patient to inhale deeply, while simultaneously contracting the abdominal muscles and keeping the mouth and throat open. The patient then holds their breath for 2 s followed by vigorous exhalation, making a “ha” sound to stimulate coughing. The patient then returns to breathing control until ready to begin another cycle. Within 1 week of the intervention, each patient in this group will receive the active cycle breathing technique twice daily administered by the same physical therapist.

The phonophoresis procedures were developed by respiratory physicians, rehabilitators, caregivers, and other stakeholders. In this study, they will be led by the same experienced respiratory physician in the hospital who will not be involved in the active cycle of breathing technique. The physician checks the equipment and prepares a sterile patch before starting. Next, acetylcysteine is placed onto the sterile patch. Patients are auscultated and marked by the same experienced respiratory physician to determine the location of sputum accumulation. The emitter and the patch with the liquid are then applied in the marked position. The frequency will be adjusted to 20 kHz, with a depth of 10 mm–150 mm and intensity of 0.8 W/cm^2^, and treatment will continue for 20 min. This procedure is performed twice a day during the intervention period. If the patient has skin burns or intolerance during the execution, stop the intervention immediately.

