#### Comparison group 1: active cycle of breathing technique

Comparison group 1 will receive the same active cycle of breathing, composed of breathing control, the thoracic expansion exercise, and forced expiration, as the intervention group. This is also performed twice daily during the 1-week intervention period, for a duration of 20 min per cycle. These patients will receive mucolytic agents by inhalation.

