#### Comparison group 2: phonophoresis

The phonophoresis conductance instrument (NAVA-01TD) is used to administer the drug in the hospitalized COPD patients, using the same mucolytic agents that are used for the intervention group. The patients will undergo phonophoresis twice daily during the 1-week intervention period for 20 min each time.

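### Control group 1 is labelled breathing technique only but is also given inhaled mucolytics, so combination versus control 1 as written compares mucolytic routes and not a combined with a single treatment

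*Protocol article*

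**What the plan says.** **Aim and label.** Study design gives the purpose as: "By comparing these three groups, we hope to explore the benefits of a combined program, compared to a single intervention". In the same paragraph, "control group 1 will receive active cycle of breathing only", and control group 2 is described as phonophoresis alone.

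**Control group 1.** The Groups section gives this arm the same breathing technique as the intervention group, twice daily for the week, and then states: "These patients will receive mucolytic agents by inhalation". The agent is not named.

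**Combination arm.** "These patients will receive both active cycle of breathing techniques and phonophoresis during the 1-week intervention period". The drug for phonophoresis is given at the end of the arm's description, under Forced expiration technique: "Next, acetylcysteine is placed onto the sterile patch". No inhaled mucolytic is mentioned.

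**Control group 2.** Phonophoresis twice daily, "using the same mucolytic agents that are used for the intervention group". Again no inhaled mucolytic is mentioned.

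**Background.** The Introduction says that COPD patients at the centre "mostly use inhalation therapy to dilute the sputum". The Abstract says that the breathing technique needs the sputum to be diluted first, usually with inhaled drugs, and that this may have limited effect.

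**Outcome.** Sputum viscosity is the first primary outcome, and the Sample size section names it as the outcome for which power is calculated.

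**The concern.** Two current statements about control group 1 cannot both be true: it receives the breathing technique alone, or it receives the breathing technique with an inhaled mucolytic. The article chose to specify each arm's content and did so inconsistently, so this is not detail that a condensed article has merely left out.

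The second statement changes what one of the two control comparisons estimates. If only control 1 inhales a mucolytic, it is not a single-intervention arm. The combination arm then differs from it by one component gained (phonophoresed acetylcysteine) and one component absent (the inhaled mucolytic).

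At stake is how that contrast is read. A null result on viscosity could mean that phonophoresis adds nothing, or that both routes of mucolytic work about equally well. A positive result would show superiority over an inhaled mucolytic given with the breathing technique. Neither result answers what phonophoresis adds to the breathing technique alone.

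**Working it through.** The plan gives no figure on this point, so the check is of arm content.

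**Step 1. Arms as written.** Let B be the breathing technique, P acetylcysteine by phonophoresis, and I an inhaled mucolytic.

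| Arm | Label in Study design | Content in Groups |
|---|---|---|
| Combination | B + P | B + P |
| Control 1 | B only | B + I |
| Control 2 | P only | P |

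Label and content agree for the combination arm and control 2. They disagree for control 1.

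**Step 2. What each contrast isolates.** Subtracting components assumes, for simplicity, that effects add.

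- By the labels: combination − control 1 = (B + P) − B = P, the effect of adding phonophoresis.
- By the Groups section: combination − control 1 = (B + P) − (B + I) = P − I, phonophoresed acetylcysteine against an inhaled mucolytic.
- Under either: combination − control 2 = (B + P) − P = B. Drug and route are the same in both arms, so this contrast is untouched.

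Without additivity the second line is still a comparison of P with I in patients who all have B. Only the arithmetic difference loses its simple form.

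**Step 3. Does background care resolve it?** If every arm inhaled a mucolytic, combination − control 1 = (B + P + I) − (B + I) = P, and the contrast would isolate phonophoresis. The Introduction makes that possible, since inhalation is usual at the centre. But no sentence extends it to the trial arms, and the only place that assigns it is control 1. On that reading the descriptions of the combination arm and control 2 would be incomplete, and control 2 would not be phonophoresis alone.

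**Step 4. Direction and size.** If the inhaled mucolytic lowers viscosity, so that I is a benefit, P − I is smaller than P. The contrast then understates the effect of adding phonophoresis. The size cannot be worked out:

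- The document gives no effect of an inhaled mucolytic on viscosity.
- The Sample size section gives an effect size of 0.4 for an analysis of variance. It does not say which arm means lie behind that value, or whether control 1 was taken with or without the inhaled drug. The planned difference may already reflect control 1 as treated, and subtracting a mucolytic effect would then count it twice.

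**The case against.** The strongest defence is that the route comparison is part of the design's rationale. The Abstract presents inhaled drugs as the usual dilution step before the breathing technique, with limited effect. The Introduction says inhalation is the usual practice at the centre, and the Discussion hopes for better drug absorption. On this view control 1 is usual practice, and the combination arm replaces the inhaled step with phonophoresis. That is a legitimate question. It is not the one stated in Study design, however, and because the inhaled agent is not named, a match of drug between the arms is not established. The defence explains the regimen but does not remove the contradiction over control 1.

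Three stronger readings are tempting, and the document does not support them.

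- **That the planned conclusion is unsupported.** The article concludes only that the combination may prove a better treatment. A win over the breathing technique with an inhaled mucolytic would support that against something close to usual practice. An effective inhaled mucolytic would also work against the combination, not towards a false claim of benefit.
- **That control 2 is compromised too.** Study design says without exception that "COPD patients will receive active cycle of breathing techniques during hospitalization". Taken literally, this would make control 2 the same as the combination. The Abstract, the phonophoresis-alone label in the same section and the description of comparison group 2 all outweigh that one general sentence. It needs clarifying, no more.
- **That a specific loss of power follows.** Any such figure would need an assumed mucolytic effect with no source in the document, subtracted from a difference that may already include it.

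**Conclusion.** The point holds as a contradiction in stated arm content with a consequence for one contrast. As written, combination versus control 1 compares phonophoresed acetylcysteine with an unnamed inhaled mucolytic, both with the breathing technique. It is not the stated comparison of a combined with a single treatment, and it does not show what phonophoresis adds.

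This rests on taking the Groups section at its word, with inhaled mucolytics in control 1 and in no other arm. If they are background care in all arms, the contrast does isolate phonophoresis, but the article would have to say so.

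The direction of the effect on viscosity is towards a smaller difference, provided the inhaled mucolytic works. Its size is not derivable. Combination versus control 2 stands. This should be fixed: it changes what one of the two control comparisons can conclude and costs little, but it does not invalidate the trial.

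**What to change.** - Reconcile Study design with the descriptions of all three arms, so that inhaled mucolytic use is stated for each arm, preferably in one table that also shows the breathing technique and phonophoresis. The sponsor decides the regimen.
- Clarify that the general sentence in Study design on the breathing technique during hospitalisation does not apply to control group 2, if that is the intent.
- If inhaled mucolytics remain in control 1 alone, drop the word only from its label. Restate the objective and conclusion for that contrast as phonophoresis-delivered versus inhaled mucolytic on top of the breathing technique.
- Record inhaled mucolytic use in all arms, whichever reading is adopted.

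The cost is protocol wording, one item on the case report form and, if the inhaled drug stays in control 1 alone, a narrower claim for that contrast.
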